#### Data collection – web-based maintenance intervention

Intervention participants will be able to access the web-based maintenance intervention using an assigned sign-up code that enables the central intervention delivery team at UoN to identify their website accesses. Access and usage data are accessible by the commercial company (GI) via website analytics, for example, Matomo Analytics. Usage data will be collected, which includes the number of visits to the website, pages viewed, duration of views on each page and the device used to access the website. Intervention participants will be able to access the website during the follow-up period of 18 months post-randomisation.

#### Data collection – interviews with selected trial participants (intervention arm)

A sub-sample of approximately 20 participants who are randomised to the REDUCE intervention arm will be interviewed at three time points: at baseline (preintervention) and approximately three and 6 months later. Baseline interviews will explore participants’ perceptions and experiences of managing DFUs pre-trial, and their hopes and expectations of the REDUCE programme and reasons for taking part in the trial. Follow-up interviews will explore participants’ engagement (or lack thereof) with the REDUCE programme’s initiation and maintenance phases, and whether this engagement leads to emotional, psychological and behavioural changes aligned with the programme’s theory (see logic model – online additional file 3). Interviews will be conducted by an experienced qualitative researcher and transcribed in full. For more information, see Hart *et al*.^30^

#### Data collection – interviews with healthcare professionals

HCPs recruited to deliver the intervention will be interviewed near to trial completion (ie, after they have delivered their last intervention session with their last participant). Interviews will explore: their experiences of the REDUCE facilitator training and delivering the one-to-one sessions (including any challenges encountered); their perspectives on the impact of the intervention on different patient-participants; their experiences of supervision and peer support and their views about the resourcing and support needed to rollout and deliver the REDUCE programme in routine clinical care. Interviews will be conducted by an experienced qualitative researcher and transcribed in full. For further information, see Hart *et al*.^31^

#### Data collection – assessing intervention fidelity

All intervention sessions will be audio-recorded. Assessment of intervention fidelity*,* that is*,* was the treatment delivered as intended, will be conducted, and it will focus on the delivery of sessions four and six. Ten per cent of randomly chosen participants, stratified by therapist, HCP profession (if appropriate) and year of trial recruitment, will be rated and 15% of these will be double rated for inter-rater reliability. The tool contains item descriptors and numerical scores. We will report overall integrity as well as component integrity. The selected sessions will be rated using the fidelity tool designed specifically for the REDUCE intervention by two skilled assessors.

### Participant payments

Patient-participants will receive a £5 shopping voucher for completion of the baseline questionnaire. A £5 voucher will be sent with each questionnaire at 6 weeks, 3 months, 6 months and 18-months post-randomisation. A final £5 shopping voucher will be sent to participants for completion of all study questionnaires at the end of the study, as a “thank you”.

### Sample size

As there is limited available data on the number of ulcer-free days on which to base a sample size, our calculation is based on the difference in percentage of participants remaining ulcer-free over follow-up. We acknowledge that it is unconventional that our sample size calculation does not match our primary analysis (ie, using a sample size calculation for proportions when the primary outcome ‘ulcer free days’ is measured as a continuous count variable). However, the approach we have adopted can be regarded as conservative as it will underestimate the power of our analysis.

Approximately 60% of patients will still be ulcer-free at 12 months^32^ (40% within 3 years). Thus, we assume that 55% of control participants will remain ulcer-free over the 18-month follow-up. Our target sample size will permit detection of a 15% increase in patients remaining ulcer-free over follow-up that is, from 55% to 70% (risk ratio=1.3). An intervention effect of this size, with 90% power and 5% significance, requires 217 patients per group (Stata V.15, χ^2^ test comparing two independent proportions). Allowing for 20% loss to follow-up increases the total sample size to 544 (ie, 272 in each group). Experience from previous trials with comparable patient groups suggests that the 20% estimate is not unreasonable. For example, the Heels trial reported 11% loss to follow-up over 6 months and Venus III 12% at 12 months.^18 33^

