## Introduction

 Diabetes affects approximately one in sixteen adults in the UK.^1^ Foot ulceration is a prevalent and costly complication, impacting up to 25% of individuals with diabetes during their lifetime.^2^ Prognosis remains poor: only 49% of people with an ulcer in England and Wales are ulcer-free (and alive) after 12 weeks of ulceration,^3^ and approximately 85% of major amputations in people with diabetes are preceded by an ulcer on the foot.^4^ Even after healing, recurrence is common, with 40% of people re-ulcerating within a year.^5^ The burden extends beyond physical health—32% of patients experience depression, which triples mortality risk.^6^ In 2014–2015, the National Health Service (NHS) expenditure on ulceration and amputation care was estimated at £837–962 million, representing 0.8%–0.9% of the budget^7^ in England.

Although the National Institute for Health and Care Excellence (NICE), the NHS, and Diabetes UK have identified improved foot care as a priority,^4 7 8^ effective preventive strategies remain limited. Current NICE recommendations emphasise risk assessment, referral and basic education, yet systematic reviews indicate education alone does not improve outcomes.^9^,^15^ Consequently, NICE has called for interventions addressing psychological and behavioural determinants, which are critical to ulcer prevention and healing.^4^

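### The claim that sizing on proportions is conservative for ulcer-free days is unsupported, and it does not hold for the only effect the sample size section specifies

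*Protocol article*

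**What the plan says.** All the sizing statements are in the protocol article, Sample size. The section says that few data exist on ulcer-free days and concedes that its calculation does not match the primary analysis. It continues: "we assume that 55% of control participants will remain ulcer-free over the 18-month follow-up". The target is 70% in the intervention arm. "An intervention effect of this size, with 90% power and 5% significance, requires 217 patients per group", from a chi-squared "test comparing two independent proportions". A 20% allowance for loss gives 272 per arm, 544 in total. The section then reassures the reader that "the approach we have adopted can be regarded as conservative as it will underestimate the power of our analysis".

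The primary outcome (Box 1) is ulcer-free days with limbs intact over 18 months. Statistical analysis plans a mixed-effects Poisson or negative binomial model for it. Box 1 adds that days can also rise through faster healing, fewer amputations or better survival. None of these effects is quantified or entered in the sample size.

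**The concern.** The sentence relies on the usual rule that a continuous or count outcome carries more information than a yes/no version of it. The rule does not carry over here. More than half of each arm is expected to sit at the maximum number of days. The treatment contrast comes from the 15% of people moved to that maximum, and each contributes only the days that an ulcer would have cost. Variation in those days adds noise that the binary endpoint lacks.

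The sentence tells readers that power for the primary outcome exceeds 90%. If it does not, a null primary result could be taken as good evidence of no worthwhile effect when the trial was less able to show one than stated.

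**Working it through.** **1. Reproduce the plan's figure.** Inputs from Sample size: 0.55, 0.70, power 90%, two-sided 5%.

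n = [1.96·√(2·0.625·0.375) + 1.2816·√(0.2475 + 0.21)]² / 0.15² = (1.3419 + 0.8668)² / 0.0225 = 216.8, so 217 per group. Then 217/0.8 = 271.25, so 272 per arm and 544 in total. The plan's arithmetic is correct.

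**2. Compare the two endpoints without assuming an ulcer duration.** Let p be the proportion ulcer-free. Among those who ulcerate, let days lost have mean m and coefficient of variation cv, the same in both arms.

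- Difference in mean days: 0.15·m
- Variance in an arm: m²·[p(1−p) + (1−p)·cv²]
- Standardised effect: 0.15 / √(average over arms of [p(1−p) + (1−p)·cv²])

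The mean m cancels, and the binary endpoint is the case cv = 0. Power is Φ(effect·√(217/2) − 1.96), with √(217/2) = 10.42.

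| cv | averaged term | effect | power |
|---|---|---|---|
| 0 (binary) | 0.22875 | 0.314 | 90% |
| 0.5 | 0.32250 | 0.264 | 79% |
| 0.7 | 0.41250 | 0.234 | 68% |
| 1.0 | 0.60375 | 0.193 | 52% |

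In this model, any spread in days lost takes power below that of the binary test.

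**3. Simulate onset, healing and recurrence.** Follow-up is 548 days, and the onset hazard is calibrated to 55% and 70% ulcer-free. The only healing figure in the document is in the Introduction: "only 49% of people with an ulcer in England and Wales are ulcer-free (and alive) after 12 weeks of ulceration". Treating healing as exponential (an assumption) gives a mean duration of 84/(−ln 0.51) = 124.8 days. Healing is equal in both arms. The test compares means.

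| Scenario, constant hazard | Mean days | Difference | SDs | Power, 217 per arm | Power, 272 per arm |
|---|---|---|---|---|---|
| Single episode | 502 vs 518 | about 16 | 80, 67 | about 59% | about 69% |
| Recurrent ulcers | 496 vs 515 | about 20 | 88, 72 | about 73% | about 82% |

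Check by formula, recurrent case: 19.7/√((88.1² + 71.9²)/2) = 19.7/80.4 = 0.245. Then 0.245·10.42 = 2.55, and Φ(2.55 − 1.96) is about 72%.

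**4. Vary the assumptions (217 per arm, comparison of means).**
- Front-loaded onset or lognormal durations at the same mean: 50-75%.
- Mean durations of 42-365 days: mostly 50-81%; the least favourable combination gave about 39%.
- Ulcers that never heal: 83-87%.
- Hazard doubled or tripled after a first recurrence: 81-87%.
- Equal 18-month mortality of 5%, 10% or 15% that cuts ulcer-free days (assumed): about 50%, 40% and 30%.

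No scenario with the stated effect alone reached 90% at 217 per arm.

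**5. Count models at the 124.8-day duration.** Negative binomial: 44% (single) and 55% (recurrent), with type I error near 2%. Poisson with robust standard errors: 61% and 71%. Poisson with model-based standard errors rejects 94-98% of the time, but its type I error is about 57-63%, so this is not usable power.

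**6. Add a healing effect.** With recurrent ulcers, healing 1.2 times faster in the intervention arm gives about 90% and 1.3 times gives about 94%. With a single episode the figures are about 83% and 91%.

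**The case against.** The strongest defence is that the day count captures what the binary endpoint misses. The Introduction gives better healing after recurrence as an aim of REDUCE, and Box 1 lists healing, amputation and survival as routes to more days. If healing were also about 1.2-1.3 times faster, the statement would be true. This part stands: a reader might infer that the claim is false in all circumstances, and the documents do not support that. But Sample size neither quantifies such an effect nor makes its claim conditional on one. A calculation that needs a second, unstated benefit is not conservative.

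A reader might also want a single power figure or a single target difference in days. The documents fix neither. The difference is about 16 days with one episode and 20 with recurrence, and the Introduction's figure also counts deaths, so it is not a pure healing time for recurrent ulcers.

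Using 217 per arm treats everyone lost as contributing nothing. The planned model uses length of follow-up, so the effective number lies between 217 and 272. At the 12-week-based duration, 272 still falls short of 90%. Covariate adjustment and centre effects were not modelled, because the document gives no figures for them. A rank test would keep about 87-91% power, but it is not the planned analysis.

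Finally, the mismatch is openly disclosed, and the plan promises 95% confidence intervals, which limit misreading of a null result. Both are fair points. Neither supports the statement about power.

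**Conclusion.** The concern holds in a limited form. The sample size arithmetic is right, and 90% power is correct for the proportion remaining ulcer-free. The further statement that this understates power for ulcer-free days has no calculation behind it and fails for the one effect specified.

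That direction follows from the algebra in step 2 when days lost per ulcerated person are similarly distributed in both arms; the simulations, which relax this, agree. The size is less certain because it depends on assumed ulcer duration, recurrence, mortality and model. Without mortality it is roughly 50-87% for a comparison of means in most scenarios, and about 44-55% for a negative binomial model at the duration set from the 12-week figure.

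This does not show that the trial is too small: an added effect on healing, amputation or survival could bring power to 90% or more.

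**What to change.** Delete the sentence on conservatism, or make it conditional on a stated additional effect on healing, amputation or survival. State that the 90% power applies to the proportion remaining ulcer-free. Report simulated power for the final primary day-count model at the actual sample size, over a labelled range of ulcer duration, recurrence, mortality and healing effect. Show the matching difference in days for each scenario rather than one fixed target.

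Trial status records that recruitment is complete, and no extra recruitment or change of outcome is proposed. The cost is about a day of simulation and some rewording; the downside is that the stated power becomes less favourable.

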### Additional studies in the REDUCE trial

Two additional studies are being implemented alongside the trial, the biological mechanisms study and a methodological trial on retention.

#### Biological mechanisms sub-study

Multiple psychological and behavioural factors have been reliably associated with DFU outcomes. This National Institute for Health and Care Research (NIHR) Efficacy and Mechanism Evaluation funded sub-study will use the opportunity of the REDUCE trial to elucidate the molecular pathways through which REDUCE and the psychological and behavioural risk factors it changes affect DFU outcomes. Please refer to Additional File 1 for details of this sub-study.

#### Methods for enhancing retention

Strategies can be included to support the recruitment and retention of participants. However, it is also important to rigorously evaluate these strategies by embedding them into clinical trials;^34 35^ also known as Studies Within A Trial (SWAT). The REDUCE trial will include a SWAT to evaluate whether sending a birthday card improves the retention of participants in trials involving an adult population. The results of the SWAT will be published following the completion of the trial. Please refer to Additional File 2 for details of this SWAT.

### Data management

Information will be held securely on paper and electronically. Security measures include appropriate storage, restricted access, and arrangements for disposal of participants’ personal and clinical details based on University of York destruction guidance. Clinical data collected within the CRFs will be processed by YTU using a licensed, automated, electronic system (Teleform), enabling data entry, checking and validation. Participant data collected within the CRFs will be processed by UoN and 10% will be checked and validated. Specific details regarding the processing of the data will be documented in a study-specific data management plan.

The study will be conducted in accordance with the Data Protection Act 2018. The trial team will ensure that participant anonymity is maintained throughout the study and following completion of the study. Participants will be identified on all study-specific documents (except for the informed consent form and enrolment log) only by the participants’ study-specific identifier. Initials will not be used in the study identifiers for the qualitative or fidelity components of the trial. The Investigator Site File will hold an enrolment log detailing the study-specific identifier alongside the names of all participants enrolled in the study.

All documents will be stored securely with access restricted to study staff and authorised personnel. At the end of the study, following completion of the end of study report, YTU will securely archive all centrally held study-related documentation in the Trial Master File for a minimum of 5 years. At the end of the defined archive period, arrangements for confidential destruction will be made.

FG will act as the custodian of the data generated from the main trial data collection.

### Statistical analysis

The primary and secondary analyses of the quantitative clinical data will be pre-specified in a Statistical Analysis Plan, which will be finalised before the end of follow-up. Analyses will be conducted in Stata V.18 or later. Treatment effects and corresponding 95% CIs will be reported, and statistical significance will be assessed at the 5% level. All outcomes will be reported descriptively at all collected time points. Continuous data will be presented using means and SD or medians and ranges as appropriate, and categorical data will be presented using frequencies and percentages.

The primary analysis will be on an intention-to-treat basis, analysing patients in the groups to which they were randomised. The number of ulcer-free days will be analysed using a mixed-effects Poisson regression model, or negative binomial model as appropriate. The model will adjust for ulcer history and other relevant baseline covariates as fixed effects. Centre will be adjusted for as a random effect. Length of follow-up will be incorporated into the model to consider participants who are lost to follow-up before 18 months post-randomisation. The total number of days spent in hospital will be analysed in a similar manner.

The proportion of participants remaining ulcer-free will be compared between the two groups using a mixed-effect logistic regression including the same fixed and random effects used in the primary analysis. Other binary secondary outcomes will be analysed in a similar manner.

Time to re-ulceration will be analysed via a Cox Proportional Hazards regression model adjusting for the same fixed and random effects used in the primary analysis. Other time-to-event secondary outcomes will be analysed in a similar manner.

Psychological/behavioural outcome measures will be analysed using mixed-effect linear regression models adjusting for relevant baseline covariates as fixed effects and centre as a random effect.

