### Study setting

This is a multi-centre RCT involving up to 30 clinical sites recruiting a total of 544 participants. It is anticipated that the participant population will be recruited from specialist multidisciplinary diabetic foot clinics at participating NHS Trusts from across the UK. The intervention will be delivered remotely by healthcare professionals (HCPs) who are independent of the participating Trusts. HCPs will be invited to take part in the process evaluation.

Usual care for both arms of the study will be provided by the clinical care teams in primary care, secondary care and community health services, including community podiatry teams.

Clinical outcome data will be extracted from any relevant healthcare records, including (but not limited to) primary care, secondary care, community health and podiatry records.

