### Randomisation

Following consent and completion of all baseline data collection and assessments, trial participants will be randomised. Participants will be told which arm they have been allocated to immediately after randomisation by a member of the unblinded local research team at the recruiting Trust where possible, otherwise they will be notified by a delegated unblinded member of the team as soon as possible.

Participants will be allocated to either:

**
*REDUCE intervention plus usual care (intervention arm)*
**
Eight weeks of 1 hour, one-to-one sessions with a HCP trained to deliver the REDUCE intervention. Participants will also be able to access the web- and/or booklet-based maintenance intervention. During the intervention period, participants will continue to receive usual standard care.
**
*Usual care alone (control arm)*
**
Participants will receive usual standard care.

The randomisation schedule will be stratified by ulcer history (one previous ulcer vs more than one previous ulcer) and formed of randomly permuted blocks of randomly varying sizes using a 1:1 allocation ratio.

Randomisation will be performed by a remote, centralised, online randomisation service provided by the York Trials Unit (YTU). Telephone backup will be available if required. The allocation sequence will be generated by a statistician not involved in the study.

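### Neither the stated models nor the sample size allows for therapist clustering in the intervention arm, where a central team of healthcare professionals cuts across centres

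*Protocol article*

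**What the plan says.** On delivery, the Study setting section states: "The intervention will be delivered remotely by healthcare professionals (HCPs) who are independent of the participating Trusts". The Study intervention section adds that one central team arranges the sessions, that each intervention participant is offered eight one-to-one sessions of about an hour, and that controls receive neither the sessions nor the materials. There is more than one therapist, because the section on assessing intervention fidelity stratifies its sample by therapist.

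On analysis, the primary model is a mixed-effects Poisson or negative binomial regression for ulcer-free days. Ulcer history and other baseline covariates are fixed effects, and then: "Centre will be adjusted for as a random effect". The logistic and Cox models for secondary outcomes reuse the same fixed and random effects. The models for psychological and behavioural outcomes again name centre. Therapist appears in none of them.

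On sample size: "we assume that 55% of control participants will remain ulcer-free over the 18-month follow-up", the target is 70% with the intervention, and "An intervention effect of this size, with 90% power and 5% significance, requires 217 patients per group". The method is given as a chi-squared "test comparing two independent proportions".

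**The concern.** This is a partially nested design. Intervention participants who share an HCP may have correlated outcomes, while each control stands alone. Because the HCPs belong to a central team and not to the Trusts, their caseloads are not nested in recruiting centres. A random intercept for centre therefore does not pick up differences between therapists.

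If such differences exist, the mean of the intervention arm is known less precisely than the model assumes. The confidence interval for the treatment effect would be too narrow and the planned power lower than stated. The same structure carries over to the secondary models, including the psychological and behavioural outcomes that the sessions target directly.

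**Working it through.** **Inputs from the protocol article (Sample size):** 55% ulcer-free in controls, 70% with the intervention, 5% significance (taken as two-sided), 90% power, 20% loss to follow-up.

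**Reproducing the plan's figure.** With pooled proportion 0.625 and no continuity correction:

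n = [1.96 × √(2 × 0.625 × 0.375) + 1.2816 × √(0.55 × 0.45 + 0.70 × 0.30)]² / 0.15² = 216.8, so 217 per group.

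217 / 0.8 = 271.25, so 272 per group and 544 in total. The stated figures reproduce exactly with no design effect, so they contain no allowance for clustering.

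**Assumptions, because the article does not give them:** number of HCPs k = 6 to 20 and therapist ICC = 0.01 to 0.05, with equal caseloads and one HCP per participant.

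**Formulas.** Only the intervention-arm variance is inflated:

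- Design effect in that arm: DE = 1 + (217/k − 1) × ICC
- SE of the difference: √[(0.2475 + 0.21 × DE) / 217]; the naive SE has DE = 1 and equals 0.0459
- Power using the correct SE: Φ(0.15/SE − 1.96)
- Type I error of the naive test when the average effect is zero but therapists differ: 2 × [1 − Φ(1.96 / √((1 + DE)/2))]

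**Worked example, k = 10 and ICC = 0.03.** DE = 1 + (21.7 − 1) × 0.03 = 1.621. SE = √[(0.2475 + 0.3404)/217] = 0.0521, which is 1.13 times the naive SE. Power = Φ(0.15/0.0521 − 1.96) = 82%. Type I error = 2 × [1 − Φ(1.96/1.145)] = 8.7%.

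| HCPs | ICC | DE (intervention arm) | True SE / naive SE | Power | Type I error of naive test |
|---|---|---|---|---|---|
| 20 | 0.01 | 1.10 | 1.02 | 89% | 5.6% |
| 20 | 0.05 | 1.49 | 1.11 | 84% | 7.9% |
| 10 | 0.01 | 1.21 | 1.05 | 88% | 6.2% |
| 10 | 0.03 | 1.62 | 1.13 | 82% | 8.7% |
| 10 | 0.05 | 2.04 | 1.22 | 77% | 11.2% |
| 6 | 0.05 | 2.76 | 1.34 | 68% | 15.3% |

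A true SE 2% to 34% larger than the naive SE means a naive SE 2% to 26% too small (1 − 1/1.022 and 1 − 1/1.344).

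**Checks.** With DE = 1 the power formula returns 90.4%, because it uses unpooled variance. The pooled version returns 90.0%, and with clustering it runs slightly lower than the table. Over a wider range (5 to 20 HCPs, ICC 0.005 to 0.05), the pooled version gives an SE ratio of 1.01 to 1.41, power of 89.3% to 61.7% and type I error of 5.3% to 17.2%. All figures use a normal approximation with no correction for a small number of therapists.

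**The case against.** Several points on the other side have force.

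- **Size is unknown.** A reader might infer that the trial's standard errors are definitely too small. The article does not support that: it gives neither the number of HCPs nor an ICC. Sessions end within 12 weeks, usual foot care comes from local teams, and outcomes are taken from healthcare records over 18 months by blinded assessors. The therapist ICC on ulcer outcomes could be close to zero.
- **Fidelity sampling is not evidence of differing outcomes.** Stratifying that sample by therapist shows that there are several therapists and that delivery is to be checked across them. It does not show that outcomes are expected to vary.
- **Type I error.** Randomisation is individual. If REDUCE affects nobody, it does not matter who delivered it, and the naive test keeps its level. Inflation needs therapists whose effects differ around an average of zero.
- **The model adjusts for more than centre.** Ulcer history and other baseline covariates are fixed effects. Centre is the only random effect named.
- **The outcome differs.** The figures above are for the binary ulcer-free proportion. The primary outcome is ulcer-free days, for which no variance or ICC is given. The Sample size section also calls its binary basis conservative for power; that could offset some of the loss, but the argument does not address clustering.
- **The nesting may not be clean.** The article does not say that one HCP gives all eight sessions, and the footnote to Table 2 foresees HCPs leaving the team.
- **The SAP is not shown.** It could add a therapist term, so a reader should not infer that the trial team has overlooked therapist effects altogether.

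These points make the size conditional and limit the claim to the model as published. They do not change the structural fact that the article sets out a clustering structure for every model, and that structure leaves out therapist.

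**Conclusion.** The point holds as a conditional one. As published, neither the analysis models nor the sample size allows for therapist clustering in the intervention arm, and the centre random effect cannot stand in for it.

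If the therapist ICC is above zero, the treatment-effect confidence interval is too narrow. Under the assumed 6 to 20 HCPs and ICC 0.01 to 0.05, on the binary outcome, the consequence runs from trivial (SE 2% larger, power 89%) to material (SE 34% larger, power 68%). The naive test's type I error of about 5.6% to 15% applies only when the average effect is zero and therapists differ. None of these figures can be carried over directly to ulcer-free days.

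The analysis should be amended, but the article does not show that the planned result would be invalid.

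**What to change.** Before the SAP is finalised, which the article places before the end of follow-up (expected by 31 March 2026), pre-specify a partially nested analysis of the primary and key secondary outcomes, at least as a sensitivity analysis:

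- a therapist random effect in the intervention arm only, alongside the centre effect;
- controls, and intervention participants who attended no session, as singleton clusters;
- a rule for assigning therapist when several HCPs were seen, for example the HCP who gave most of the sessions;
- a small-sample correction if therapists are few;
- the estimated therapist ICC reported with the results.

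Also state that the 90% power makes no allowance for therapist clustering. Recruitment closed on 27 September 2024, so for the sample size only this caveat is possible.

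The cost is mainly SAP wording and model code. HCPs already record data for every scheduled session, so therapist identity should be recoverable, though this needs confirming. The confidence interval will widen if the ICC is not negligible. With few therapists the variance component will be imprecise and the crossed count model may be hard to fit, which is a fair reason to keep it as a sensitivity analysis.
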